**Figure 1 fig1:**
[figure not shown]
Design of patient 6 visits throughout the study.

An initial visit at the pharmacy will be performed (in person) with the participants (visit 2). During this visit, the investigator pharmacist from Blanquerna will obtain the signed informed consent, collect basic sociodemographic data (age, weight, height, and gender), and will perform the nutritional and well-being questionnaires and duration of current medication. Further, information about the personal trainer, the training schedule and the corporate Teams meeting links and password will be provided. During the first meeting, the participant will be provided with: the recommendations for a healthy diet by the Spanish Society of Diabetes and a nutritional proposal based on the abovementioned guidelines (33).

Two additional monthly check-ups, consisting of a short telephone interview (covering any adverse events, general well-being, etc.) will be performed 2 and 3 months after study initiation (visit 3 and visit 4).

A final visit at month 4 (visit 5), will be performed at the end of the study, in the pharmacy office where the well-being questionnaire and a satisfaction questionnaire will be provided. Upon completion of the study at the pharmacies, a second blood test at CAP Sant Rafael will be requested by the CAP physician; this procedure will take place during the 6th visit.

Pharmacists will oversee the follow-up, to ensure safety through rigorous monitoring and reporting procedures. Any concerning findings will be promptly addressed, and appropriate measures will be taken to safeguard participant health and ensure the integrity of the study results.

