### Participants

2.2

The study will include a total of 80 individuals of both sexes (female, male) with a diagnosis of T2D. Among them, 40 individuals will be required to be on a VitD treatment for at least, 6 months, for reasons recommended by the ECAP working group (including osteoporosis, osteopenia, and VitD deficiency), and the other 40 will not be receiving VitD supplementation.

Subjects will be recruited during usual medical care in a convenience-based by the collaborating physician from the Primary Care Center (CAP) Sant Rafael in Barcelona, Spain.

During the initial visit with the physician at CAP Sant Rafael, participants will be provided with the Patient Information Sheet and the Informed Consent and subsequently will be asked to provide their preferred contact information (phone number or email). This information will be used by the principal investigators from Blanquerna to reach out explaining the study with detailed instructions (explaining the patient information sheet and address any questions they may have). After receiving the information and clarifying any potential concerns, participants will be asked to sign the informed consent.

After enrollment and stratification by VitD treatment status, participants will be randomized within each stratum to exercise intervention or to no exercise. An independent investigator, not involved in recruitment or outcome assessment, will generate the randomization sequence using a computer-based block randomization method within VitD strata. Allocation will be implemented via a secure, web-based central randomization system accessible only after completion of baseline assessments and confirmation of eligibility. This ensures that the four groups (see Table 1) are balanced and clearly defined as: Group 1, Exercise + VitD users; Group 2, Exercise + VitD non-users; Group 3, VitD only (no exercise); and Group 4, Control (no VitD & no exercise).

**Table 1 tab1:** Group allocation of participants with T2D.

Group	VitD treatment status	Exercise intervention	*n*
1	On VitD ≥ 6 months	Exercise program	20
2	No Vit D treatment	Exercise program	20
3	On VitD ≥ 6 months	No exercise	20
4 (Con)	No Vit D treatment	No exercise	20

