### Sarcoplasm-stimulating training program

2.7

A sarcoplasm-stimulating training program will be used as the primary intervention model. This program combines resistance and aerobic components with short rest intervals between sets, designed to increase metabolic stress and enhance both muscular endurance and insulin sensitivity. Such adaptations are particularly relevant in patients with T2D, where resistance training has been shown to improve glycemic control, body composition, and inflammatory status (6, 8, 20). In addition, this training format can be implemented safely in an online, home-based setting without the need for specialized equipment, making it feasible and scalable in real-world primary care contexts.

This is a home training program where sessions are conducted online via corporate Teams from Blanquerna, Universitat Ramon Llull. Participants will not require any additional material, as the physical activity program has been specifically designed to be performed without equipment. Participants will receive in person by the investigator and personal trainer, the link and access codes during their initial visit to the community pharmacy.

The program consists of one familiarization week followed by three progressive 5-week phases (weeks 1–15), each with gradually increasing intensity and reduced rest intervals (see Table 2). In Week 1 after familiarization, participants will perform 4 sets of 8 repetitions at 60% of 1RM, with 20 s of rest between sets. In Week 2, the same format will be maintained with slightly higher intensity (65% 1RM). In Week 3, each movement will be performed in 5 sets of 6 repetitions at 75% of 1RM, with 20 s of rest. In Week 4, the number of sets and repetitions will be maintained but the intensity of training will increase to 80% of 1 RM. In Week 5, considered a tapering phase, participants will perform 5 sets with 4 repetitions at 70% of 1RM, again with 20 s of rest between each set. This 5-week progression will be repeated and advanced through Weeks 6–10 and Weeks 11–15.

**Table 2 tab2:** Distribution of the sarcoplasm-stimulating training program (weeks 1–15).

Phase	Week	Sets × repetitions	Rest interval (seconds)	Intensity (% 1RM)
Familiarization	–	Technique practice, no external load	–	–
Phase 1	1	4 × 8 reps	20	60%
	2	4 × 8 reps	20	65%
	3	5 × 6 reps	20	75%
	4	5 × 6 reps	20	80%
	5 (taper)	5 × 4 reps	20	70%
Phase 2	6	4 × 8 reps	20	60%
	7	4 × 8 reps	20	65%
	8	5 × 6 reps	20	75%
	9	5 × 6 reps	20	80%

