### Participant visits and follow-up

2.9

A total of 6 visits are expected per each participant. The study includes a first visit at the designated CAP for the explanation of the study, right before the intervention. During this first visit, physicians from CAP Sant Rafael will thoroughly assess participants to confirm their eligibility for the study. During the initial visit, the physicians will provide potential participants with the Patient Information Sheet and the Informed Consent allowing them time to review the documents at home. During this first visit, participants will be asked to provide their preferred contact information (phone number or email), which will be later used to send detailed instructions, the list of participating pharmacies, and to initiate their participation in the study. Blanquerna investigators will explain the study protocol using the patient information sheet and will set a meeting at the community pharmacy. Pharmacies will collaborate solely by providing the space, while all study activities will be conducted by the investigator’s pharmacist from Blanquerna.

Once the patients signed the informed consent, blood samples will be requested by the physicians from CAP Sant Rafael for clinical analysis; this analysis will take place during the second visit at the CAP.

The collaborating community pharmacies from the geographical area of the study can be seen in Table 3.

**Table 3 tab3:** Collaborating pharmacies near CAP Sant Rafael.

Pharmacy	Contact information
[name]	[name]. [contact]
[name]	[name]. [contact]
[name]	[name]. [contact]
[name]	[name]. [contact]
[name]	[name]. [contact]
[name]	[name]. [contact]
[name]	[name]. [contact]
[name]	[name]. [contact]
[name]	[name]. [contact]
[name]	[name]. [contact]
[name]	[name]. [contact]
[name]	[name]. [contact]
[name]	[name]. [contact]
[name]	[name]. [contact]

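### As most naturally read, session access is handed over at pharmacy visit 2, before the baseline blood sample and therefore before section 2.2 allows allocation

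*Protocol article*

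**What the plan says.** Four statements in the protocol article bear on when participants gain access to the online exercise sessions.

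- **Allocation (section 2.2).** After stratification by vitamin D status, "participants will be randomized within each stratum to exercise intervention or to no exercise". The allocation system is "accessible only after completion of baseline assessments and confirmation of eligibility".
- **Consent and hand-over (section 2.9).** At the first pharmacy visit, numbered visit 2, the investigator pharmacist "will obtain the signed informed consent", records basic data including weight and height, and administers the nutritional and well-being questionnaires. Trainer details are given at this visit, and "the training schedule and the corporate Teams meeting links and password will be provided". The sentence does not limit this to the exercise groups.
- **Hand-over again (section 2.7).** Participants receive "the link and access codes during their initial visit to the community pharmacy", in person, from the investigator and the trainer.
- **Baseline blood (section 2.9).** "Once the patients signed the informed consent, blood samples will be requested by the physicians from CAP Sant Rafael for clinical analysis". The draw is placed at the second attendance at the primary care centre (CAP), not at the pharmacy.

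Section 2.4.1 makes change in HOMA-IR the primary endpoint. Section 2.11 uses baseline HOMA-IR as the ANCOVA covariate.

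**The concern.** Exercise against no exercise is the only randomised factor, since vitamin D status is pre-existing. The programme is live, online and needs no equipment, so a link and a password are enough to take part. The time at which those are released, and to whom, is therefore part of keeping the arms apart.

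If access is released before allocation, future controls hold the means to join. Any who do would dilute the exercise contrast toward zero. If instead only exercisers receive access at visit 2, participants know their arm before the fasting sample that gives baseline HOMA-IR. They could then change behaviour or withdraw before baseline is complete. That is what the rule in section 2.2 is there to prevent.

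**Working it through.** No figure in the plan is at issue. The check is to put the stated steps in order.

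1. **Visit 1, CAP (section 2.9).** Eligibility is assessed, the information sheet and consent form are given to take home, and a phone number or e-mail address is collected.
2. **Visit 2, pharmacy (sections 2.7 and 2.9).** Signed consent is obtained, questionnaires and basic measurements are done, and the schedule, links and password are handed over.
3. **Baseline blood, CAP (sections 2.5.4 and 2.9).** This is requested once consent is signed and drawn before the intervention. If consent is signed at visit 2, the draw follows visit 2.
4. **Allocation (section 2.2).** This is possible only when baseline assessments are complete, so after step 3.

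On this order the hand-over in step 2 precedes the allocation in step 4. Two outcomes are possible:

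- **Section 2.2 is followed.** Nobody is allocated at visit 2, so access goes to people whose arm is unknown. By Table 1, Groups 3 and 4 will hold 20 + 20 = 40 of the 80 participants, and those 40 are meant to have no exercise programme.
- **Access at visit 2 is limited to exercisers.** Allocation must then be known at visit 2, before the blood sample, which section 2.2 does not allow.

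The step from 2 to 3 is an inference, so the visit numbering was checked. Section 2.9 expects six visits: visit 1 at the CAP, visit 2 at the pharmacy, visits 3 and 4 by telephone, visit 5 at the pharmacy, and visit 6 for the final blood test. All six numbers are used and none belongs to the baseline draw. The numbering therefore neither confirms nor excludes a draw before visit 2. The consent sequence is the only textual guide, and it points to a draw afterwards.

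**The case against.** The strongest reply is that the protocol nowhere says the blood draw follows the pharmacy visit. Section 2.5.4 only places it after the first visit and before the intervention. Participants take the consent form home, and section 2.2 asks them to sign after the investigators have explained the study, without naming the pharmacy. Obtaining the signed form at visit 2 could mean collecting one signed earlier. Blood could then come before visit 2, allocation could be made during visit 2 after the questionnaires, and links could go to exercisers at the end. This would satisfy section 2.2. It cannot be excluded, and Figure 1 might show it. But it needs an allocation step within visit 2 that the text does not describe, and it is not the natural reading of consent being obtained there.

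Three further points have weight:

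- Section 2.7 describes the training programme, so its participants may be exercisers only. A reader might infer that the plan means to give all 80 people the codes. The documents do not support that: section 2.9 leaves out a restriction, which is not the same as intending none. This does not settle when allocation becomes known.
- Section 2.7 says sessions are live and the trainer monitors attendance, so a control who joined could be noticed. This reduces the contamination risk. The protocol does not say what would then be done.
- HOMA-IR is computed from a fasting laboratory sample and is less open to bias from a known arm than self-report. Changed behaviour and withdrawal remain possible.

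That a condensed article leaves logistics to the full protocol is not a sufficient answer here. The article states the timing of hand-over twice, and also the timing of consent and of allocation. The difficulty lies in how these statements fit together.

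**Conclusion.** The point holds at moderate confidence. On the most natural reading, sections 2.2, 2.7 and 2.9 cannot all be followed with access confined to the exercise arms and allocation withheld until baseline is complete. This rests on one assumption: that consent is signed at visit 2, so that the baseline blood comes after it.

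The harm is a risk and its size is not known. A reader might be tempted to turn it into a loss of power by assuming that some share of controls joins the sessions. The documents do not support such a figure. They give no crossover rate, the benefit to a control who joins is unknown, and section 2.2 sizes the trial with a model for a proportion, so no starting power for HOMA-IR is established. Nor should the conflict be called proven, given the missing figure and the unnumbered baseline draw.

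It is still worth correcting, because it touches the only randomised comparison and the remedy is small.

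**What to change.** Reconcile sections 2.2, 2.7 and 2.9 by stating one order of events:

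1. consent and baseline questionnaires;
2. baseline blood, with its own place in the visit schedule;
3. central randomisation;
4. release of the training schedule, links and password to Groups 1 and 2 only.

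Release can use the phone or e-mail contact already collected at visit 1. If the investigators prefer a hand-over in person, it can stay, provided allocation is made after all baseline assessments, including blood, are complete. Sections 2.7 and 2.9 should both say that access is for the exercise groups only.

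The cost is protocol wording and one contact after randomisation in place of the hand-over at visit 2. The sample size and the analysis do not change.

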### Safety

2.10

Measures to ensure the safety of participants include a thorough medical screening prior to enrollment, and a close monitoring of patients’ health status during intervention. Safety protocols also include the role of participating healthcare centers in case of any medical concerns or emergencies during the trial.

All adverse events, including hypoglycemia, hyperglycemia, musculoskeletal injuries, fatigue, and any other exercise-related symptoms, will be systematically collected. Adverse events will be assessed at each training session, at each pharmacy follow-up visit, during monthly telephone interviews, and at the final visit. The type, severity, and potential relation to the intervention will be documented. Serious adverse events will be reported immediately to the study’s principal investigators and the Ethics Committee. No interim efficacy analysis is planned due to the exploratory nature of this trial; however, the study will be stopped if ≥20% of participants in any arm experience serious adverse events related to the intervention.

In addition, participants will be provided with information on participating community pharmacies to receive appropriate assistance if needed. Additionally, participants will be educated on signs and symptoms of hypo-and hyperglycemia and instructed on appropriate actions to take if these occur during or after exercise sessions. The trial protocol also includes provisions for modifying or discontinuing exercise interventions based on individual participant responses and safety concerns identified during the trial.

Physical activity is not expected to produce adverse events. Nonetheless, physical activity programs will be individualized based on the needs and characteristics of each participant. If any adverse events related to physical activity are detected, patients can go to healthcare centers following standard practice.

### Statistical analysis

2.11

All data will be reported as mean and standard deviation. Data normality and homogeneity of variance will be tested using Shapiro–Wilk and Levens tests, respectively. The primary endpoint (change in HOMA-IR) from baseline to 16 weeks, will be analyzed using ANCOVA with group as the fixed factor, baseline HOMA-IR as covariate, and VitD treatment status included as a stratification variable. Secondary continuous outcomes (glycemic, lipid, inflammatory, anthropometric, dietary, and psychological well-being measures) will also be analyzed with ANCOVA, adjusting for baseline values. Categorical outcomes (e.g., adverse events) will be compared using χ^2^ or Fisher’s exact test. Bonferroni *post hoc* test will be used if there is a significant difference between the groups. Exploratory analyses will test for interaction effects between exercise and VitD status using factorial ANOVA models; these analyses are considered hypothesis-generating due to sample size limitations. In addition, exploratory analyses will be performed to examine potential sex-related differences in primary and secondary outcomes. Sex will also be included as a covariate in the statistical models when appropriate. Statistical power will be calculated by *post hoc* power analysis method by using G Power software.

The results will be analyzed using SPSS (version 22) for Windows. The significant level (*α*) of all statistical analyses will be 0.05.

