We hypothesize that the combination of aerobic and resistance training with ongoing VitD treatment will lead to greater improvements in insulin resistance (primary endpoint: HOMA-IR) compared with exercise alone, VitD alone, or control (no intervention). Secondary hypotheses are that exercise, with or without VitD, will also improve glycemic control, lipid profile, body composition, inflammatory markers, diet adherence, and psychological well-being.

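### The primary ANCOVA contains both the four-level group factor and VitD status, which group already determines, so the group test that gates the post hoc comparisons can have 2 or 3 degrees of freedom

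*Protocol article*

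**What the plan says.** - **Primary model (section 2.11).** The change in HOMA-IR to week 16 "will be analyzed using ANCOVA with group as the fixed factor, baseline HOMA-IR as covariate, and VitD treatment status included as a stratification variable".
- **Definition of group (section 2.2 and Table 1).** The four groups cross VitD status with exercise: "Group 1, Exercise + VitD users; Group 2, Exercise + VitD non-users; Group 3, VitD only (no exercise"), and Group 4 has neither. Each has 20 participants.
- **What is randomized (section 2.2).** After stratification by VitD use, "participants will be randomized within each stratum to exercise intervention or to no exercise". VitD use is a pre-existing characteristic.
- **Primary hypothesis (end of the Introduction).** The combination improves HOMA-IR more when "compared with exercise alone, VitD alone, or control (no intervention"). In Table 1 numbering this is Group 1 against Groups 2, 3 and 4. Section 2.1 frames superiority in the same way.
- **Post hoc step (section 2.11).** A Bonferroni "test will be used if there is a significant difference between the groups".
- **Interaction (section 2.11).** "Exploratory analyses will test for interaction effects between exercise and VitD status using factorial ANOVA models", labelled hypothesis-generating.

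**The concern.** A stratification variable normally belongs in the model beside the treatment factor. Here, however, group is not the randomized treatment: it is treatment crossed with the stratification variable. Knowing a participant's group tells you their VitD status, so entering both gives the model a redundant term.

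Two things are at stake. First, the overall group test comes before the Bonferroni comparisons, and the sentence does not settle which hypothesis it tests or on how many degrees of freedom. Second, two of the three comparisons in the primary hypothesis cross VitD strata, so their values depend on whether they are read as group coefficients adjusted for VitD or as differences between adjusted cell means. The protocol does not say which. Section 3.1 concedes that blinding is restricted, which is a further reason to settle this before outcome data are seen.

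**Working it through.** The plan states no rank or degrees of freedom to reproduce. Its only relevant figure is the total of 80, which agrees with Table 1 (4 × 20). The result below does not depend on how 80 was derived.

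**Inputs.** Four groups of 20 (Table 1); Groups 1 and 3 are VitD users, Groups 2 and 4 are non-users; model terms as in section 2.11.

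**Step 1: the redundancy.** The user indicator equals I(Group 1) + I(Group 3), and the non-user indicator equals I(Group 2) + I(Group 4). Both are exact sums of group indicators. The dependence runs one way: VitD status does not determine group.

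**Step 2: rank and degrees of freedom.**

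| Terms (with intercept) | Rank |
|---|---|
| baseline | 2 |
| VitD + baseline | 3 |
| group + baseline | 5 |
| group + VitD + baseline (as written) | 5 |
| exercise + VitD + exercise × VitD + baseline | 5 |

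- VitD given group and baseline: 5 − 5 = 0 df.
- Group given baseline: 5 − 2 = 3 df.
- Group given VitD and baseline: 5 − 3 = 2 df.
- Residual: 80 − 5 = 75 df.

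The two group tests have different null hypotheses. The 3-df test asks whether all four adjusted means are equal. The 2-df test asks only whether Group 1 equals Group 3 and Group 2 equals Group 4, that is, no exercise effect in either stratum.

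**Step 3: the hypothesis contrasts.** Write g for group effects, v1 for users and v0 for non-users. At a fixed baseline value:

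- 1 vs 3 = (g1 + v1) − (g3 + v1) = g1 − g3
- 1 vs 2 = (g1 + v1) − (g2 + v0) = (g1 − g2) + (v1 − v0)
- 1 vs 4 = (g1 + v1) − (g4 + v0) = (g1 − g4) + (v1 − v0)

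Add any constant c to g1 and g3 and subtract it from v1. Every fitted value stays the same, but g1 − g2 and g1 − g4 each move by c. Those coefficient differences are not estimable. The full cell-mean differences on the left do not move, so they are estimable. A row-space check confirms this: g1 − g3, g2 − g4 and both full differences pass; g1 − g2, g1 − g4 and v1 − v0 fail.

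**Step 4: numerical illustration** on one simulated data set of 4 × 20. This checks the algebra and forecasts nothing about the trial.

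| Contrast | Group + baseline | As written, adjusted cell means | As written, group coefficients only (one arbitrary solution) |
|---|---|---|---|
| 1 vs 2 | −0.338 | −0.338 | −0.130 |
| 1 vs 3 | −0.294 | −0.294 | −0.294 (g1 − g3 is unique) |
| 1 vs 4 | −0.580 | −0.580 | −0.372 |

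Fitted values are identical with and without VitD. The sum of squares for group is 3.376 on 3 df given baseline, and 1.438 on 2 df given VitD and baseline. VitD given group is zero.

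**Step 5: the interaction.** The exercise × VitD contrast, (g1 − g3) − (g2 − g4), is estimable in the primary model with baseline included, so no separate model is needed for it.

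**Step 6: what randomization supports.** 1 vs 3 lies within a stratum and is randomized. 1 vs 2 compares VitD users with non-users, both exercising, and is observational. 1 vs 4 = (1 vs 3) + (3 vs 4): a randomized part plus a comparison of users with non-users.

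**The case against.** **The model may be full rank.** If group means exercise versus no exercise, the sentence describes an ordinary stratified ANCOVA of rank 4 with no redundancy. Section 2.2 randomizes exercise within strata and section 2.13-type detail is not needed to see the appeal: the sample size text in section 2.2 speaks of main effects. This reading is possible but fits poorly. Table 1 numbers the groups 1 to 4, a Bonferroni step has nothing to do with two levels, and an additive two-factor model does not estimate the three hypothesis contrasts as separate quantities. Section 2.3 adds a third usage, calling VitD users the intervention group and non-users the control group. At the least, group needs a definition in section 2.11.

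**The comparisons are not lost.** A reader might infer from the rank deficiency that the primary comparisons cannot be estimated. The documents do not support that. 1 vs 3 is estimable as the model stands, and 1 vs 2 and 1 vs 4 are recovered unchanged as adjusted cell-mean differences or by dropping the redundant term. This part of the objection stands in full and limits the defect to ambiguity.

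**The additive exercise effect is not the stated target.** Because only exercise is randomized, a reader might infer that the primary estimate should become the exercise coefficient from exercise + VitD + baseline. That would change the estimand. The Introduction and section 2.1 ask whether the combination beats each alternative, and an additive model would force 1 vs 2 and 3 vs 4 to be the same number.

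**Limits on scope.** Section 2.11 does not say that baseline is left out of the factorial ANOVA, and that analysis is exploratory, so no loss of precision is claimed. For secondary outcomes section 2.11 names no VitD term, so the redundancy does not extend to them. Nothing in the protocol says that an analyst would choose between tests after seeing data; the wording only leaves that open.

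**Conclusion.** The point holds as a mis-specified primary model. With the four groups of Table 1, VitD status adds 0 df, the group test has 2 or 3 df depending on how the redundant term is handled, and 1 vs 2 and 1 vs 4 are aliased with VitD when read as VitD-adjusted group effects. Their values as adjusted mean differences are unaffected, as is 1 vs 3.

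The conclusion rests on reading group as the four cells of Table 1, which the post hoc step and the three-way hypothesis both support. It needs no assumption about variances, correlations or effect sizes. Repairing the rank does not change the status of the contrasts: 1 vs 2 stays observational and 1 vs 4 partly so under any model.

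**What to change.** In section 2.11:

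1. Define group and state one full-rank primary model. Either use four-level group + baseline HOMA-IR, or equivalently exercise + VitD stratum + exercise × VitD + baseline HOMA-IR. Both have rank 5, 75 residual df, 3 df between groups and the same fitted values.
2. Name the contrasts 1 vs 2, 1 vs 3 and 1 vs 4 as differences in adjusted means. In the factorial form with 0/1 coding they are VitD + interaction, exercise + interaction, and exercise + VitD + interaction.
3. If the overall test continues to gate the Bonferroni comparisons, state its null hypothesis and degrees of freedom (3 df for equality of the four adjusted means).
4. Take the exploratory interaction test from this same baseline-adjusted model instead of a separate factorial ANOVA.
5. State that only exercise is randomized, so 1 vs 2 is an observational contrast and 1 vs 4 is partly so.

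The cost is a few sentences in section 2.11. No new data, visits or participants are needed, and the stated hypothesis is kept.

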The sample size for this study was determined using the GRANMO program with the model of observed proportions with respect to a reference. For the calculation, it has been taken into account that the insulin resistance is the key to calculating the effects of aerobic and resistance training on clinical parameters in patients with T2D. The calculation has been made accepting an 𝜶 risk of 0.05 and a beta risk of less than 0.2 in a two-sided contrast. Based on preliminary data, there is a difference of HOMA-IR of -0.14% after 12 weeks of intervention (21). Although modest, this effect size has been reported as clinically relevant in previous clinical trials (22–24). It is assumed that the proportion in the reference group is 0.0139 (5.3 million people in Spain) (25). The percentage of necessary replacements has been predicted to be 20%. The present study is designed as an exploratory factorial randomized clinical trial; while not powered for a definitive test of interaction effects, the chosen sample size allows us to detect main effects with adequate power while providing preliminary evidence of potential interactions.

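### The exercise-by-VitD interaction model in section 2.11 names no baseline covariate, an avoidable loss of precision on the trial's least precise contrast

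*Protocol article*

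**What the plan says.** All the model statements stand in one paragraph of the protocol article, section 2.11 (Statistical analysis).

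- **Primary endpoint** (change in HOMA-IR to week 16): "analyzed using ANCOVA with group as the fixed factor, baseline HOMA-IR as covariate, and VitD treatment status included as a stratification variable".
- **Secondary continuous outcomes**: these "will also be analyzed with ANCOVA, adjusting for baseline values".
- **Interaction**: "Exploratory analyses will test for interaction effects between exercise and VitD status using factorial ANOVA models". Its status follows at once: "these analyses are considered hypothesis-generating due to sample size limitations".
- **Other covariates**: "Sex will also be included as a covariate in the statistical models when appropriate". Baseline is not mentioned again.

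The sample-size text in section 2.2 (Participants) concedes that the trial lacks power for a definitive interaction test, but still counts on it "providing preliminary evidence of potential interactions". The same section opens allocation only once baseline assessments are complete, and randomises to exercise or no exercise within VitD strata.

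**The concern.** The paragraph names ANCOVA with a baseline value twice and then switches to ANOVA for the interaction. An ANOVA in the usual sense has no continuous covariate. Baseline HOMA-IR is drawn in every participant before the intervention (section 2.5.4) and before allocation, so nothing stands in the way of using it.

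The contrast matters because the Introduction and Discussion set out to learn whether exercise and VitD merely add up or reinforce each other. Only the exercise-by-VitD interaction separates those two possibilities. It is also the contrast with the largest standard error in a 2×2 layout, so it can least afford to leave explained variance in the error term. Low power is a reason to use the baseline value there.

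**Working it through.** **Inputs.** From the documents: 80 participants in four cells of 20 (Table 1); two-sided α of 0.05 and power of at least 80% (section 2.2); the endpoint is change from baseline (sections 2.4.1 and 2.11). The article gives no SD for HOMA-IR, no correlation r between baseline and week 16, and no power figure for the interaction, so there is no stated figure to reproduce. I assume equal variance s² at both times, a common baseline slope, and r between 0.3 and 0.9. Effects are in units of s.

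**1. Is the interaction the least precise contrast?** With 20 per cell, in residual SD units:
- exercise main effect (40 v 40): √(2/40) = 0.224
- pairwise group difference (20 v 20): √(2/20) = 0.316
- interaction (difference of differences over four cells): √(4/20) = 0.447

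Yes. Its standard error is twice that of a main effect.

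**2. Residual variance under each model.**
- ANOVA on change: 2(1−r)s²
- ANCOVA with baseline: (1−r²)s²
- Ratio: 2(1−r)/[(1−r)(1+r)] = 2/(1+r)

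The ratio of standard errors is √[2/(1+r)]. In a finite sample, ANCOVA pays a small price for estimating the slope, taken here as a factor √(1 + 1/74) on its standard error, and its residual degrees of freedom fall from 76 to 75.

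| r (assumed) | Variance ratio | SE excess, large sample | SE, ANOVA on change | SE, ANCOVA (finite sample) | SE excess, finite sample | Power for an illustrative 0.8 SD interaction, ANOVA / ANCOVA |
|---|---|---|---|---|---|---|
| 0.3 | 1.54 | 24% | 0.529 | 0.429 | 23% | 32% / 45% |
| 0.5 | 1.33 | 15% | 0.447 | 0.390 | 15% | 42% / 53% |
| 0.6 | 1.25 | 12% | 0.400 | 0.360 | 11% | 51% / 59% |
| 0.7 | 1.18 | 8% | 0.346 | 0.322 | 8% | 63% / 69% |
| 0.8 | 1.11 | 5% | 0.283 | 0.270 | 5% | 80% / 83% |
| 0.9 | 1.05 | 3% | 0.200 | 0.196 | 2% | 98% / 98% |

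Power is from the noncentral t distribution. Simulation (4,000 trials) agrees: the empirical SE was 0.449 for change against 0.389 for ANCOVA at r = 0.5, and 0.352 against 0.326 at r = 0.7. Type I error was about 5% in each model.

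**3. Minimum detectable interaction at r = 0.6** (80% power, multiplier 1.960 + 0.842 = 2.802, large-sample SE):
- ANOVA on change: 2.802 × √0.80 × 0.447 = 1.12 SD
- ANCOVA: 2.802 × √0.64 × 0.447 = 1.00 SD

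The variance ratio of 1.25 means that the unadjusted test does the work of an adjusted one on 80/1.25 = 64 participants.

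**4. Is the adjusted test available at no cost in data?** The four-level group factor in the primary ANCOVA spans all four cell means; adding VitD status leaves the rank at 4. The baseline-adjusted interaction is therefore already a one-degree-of-freedom contrast of the primary model.

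**The case against.** The best defence is that the article never says baseline is left out. It names a model type and lists no terms, sex may enter the models as a covariate, and a fuller plan could add baseline. That is fair: the omission is read from the change of name. But the article does fix the name, straight after using ANCOVA with baseline twice. If adjustment is meant, the name is wrong and the same edit is needed.

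Second, the main hypothesis is a set of comparisons between groups, and these come from the primary ANCOVA, which does adjust. The interaction is openly exploratory and conceded to lack power. This stands in full and limits the weight of the point.

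A reader might also infer more than the documents support:

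- **That chance baseline imbalance biases the interaction.** It does not, because exercise is randomised within VitD strata. At r = 0.6, a typical imbalance of 0.447 SD in the contrast moves a change-score estimate by 0.4 × 0.447 = 0.18 SD. That movement is part of the excess variance already counted above, not a further harm.
- **That far more precision is lost, as with an ANOVA on week-16 values.** The endpoint is defined as change, and the article nowhere proposes an analysis of raw final values.
- **That two conflicting exercise effects will be reported.** The factorial model is stated only as a test of interaction; no main effect is promised from it.

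**Conclusion.** The point holds as one of efficiency and consistency. Section 2.11 assigns the interaction to a model with no named baseline term while adjusting every other continuous analysis in the paragraph. The estimate stays unbiased. Its standard error is larger than it need be by about 15% at r = 0.5, falling to 5% at r = 0.8 and 2–3% at r = 0.9. These figures rest on the assumed r, on equal variances at the two times and on 20 completers per cell. With 16 per cell the percentage excess is almost unchanged (11% at r = 0.6), though both standard errors grow.

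Adjustment does not rescue the test. At r = 0.6 the detectable interaction falls only from about 1.12 to 1.00 SD, so the hypothesis-generating label remains right under either model. The primary analysis is unaffected. The change is worth making because it is nearly free and falls on the one contrast that bears on synergy.

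**What to change.** In section 2.11, replace the factorial ANOVA with factorial ANCOVA models containing exercise, VitD stratum, exercise × VitD stratum, and the baseline value of the outcome being analysed. Report the interaction as an adjusted difference of differences with its 95% CI, and keep the hypothesis-generating label.

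With baseline in the model, the interaction estimate is the same whether the outcome is entered as change or as the week-16 value, so that choice no longer matters. The test can equally be taken as a contrast from the primary ANCOVA.

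Cost: one phrase, one residual degree of freedom (76 to 75), no new data and no change to the sample size.
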